## Abstract

**Background:**

In developing countries, accessibility to specialists, and physician to patient contact time is limited. In Thailand, A unique community health service is provided by subdistrict health care officers and Village Health Volunteers (VHVs). If the personnel were trained on proper chronic kidney disease (CKD) care, CKD progression would be delayed.

**Methods/Design:**

We conducted a community-based, cluster randomized controlled trial at Kamphaeng Phet Province, located about 400 kilometers north of Bangkok. Two out of eleven districts of the province were randomly selected. Approximatly 500 stage 3–4 CKD patients from 2 districts were enrolled. Patients in both groups will be treated with standard guidelines. The patients in intervention group were provided the additional treatments by multidisciplinary team in conjunction with community CKD care network (subdistrict health care officers and VHVs) which will provide group counseling during each hospital visit and quarterly home visits to monitor dietary protein and sodium intake, blood pressure measurement and drug compliance. Duration of the study is 2 years. The primary outcome is the difference of rate of eGFR decline. The secondary outcomes are laboratory parameters and incidence of clinical endpoints such as mortality rate and cardiovascular events, end-stage renal disease (ESRD), etc.

**Discussion:**

Insights of this study may set forth a new standard of community-based CKD care.

**Trial registration:**

NCT01978951.

## Background

According to a recent community-based survey among Thais, the prevalence of pre-dialysis (stage 3, 4 and 5) CKD was 8.8% [1]. It is estimated that the total number of stage 3–4 CKD patients in Thailand is 4.1 millions. With only 450 active nephrologists, the ratio of CKD patients to nephrologists in Thailand is as high as 1:15,000. The high ratio indicates that accessibility to nephrologist may not be equal for all CKD patients. At present, Thai CKD care is still based on conventional method in which a hospital-based, physician-oriented approach provided at the out-patient department [2-4]. In rural areas where physician-to-patient contact time is more limited and renal specialists are scarce or not existing, this kind of health care service is impractical. Thus, it is mandatory to seek other appropriate forms of renal care to delay CKD progression.

Thailand is geographically divided into 77 provinces. Each is divided into 5–10 districts and further into 5–10 subdistricts per district. In general, a typical subdistrict consists of 10–15 villages, each consists of 100–150 households. At the district level, there is one district hospital consisting of 3–5 general practioners providing all basic medical services including maternal and child health care, simple trauma, diabetes and hypertension. There is one subdistrict health care office in each subdistrict, with 1–2 nurses, 3–5 subdistrict health care officers, and 100–120 village health volunteers (VHVs). Healthcare personnel of each subdistrict involved in various community health activities, for example, anti-smoking campaign, HIV prevention, etc.

The VHVs are villagers voluntarily recruited from their own villages. Each VHV is responsible for 10–15 households. They work as a bridging point between villagers and health care personnel at the subdistrict health offices or district hospitals. At the moment, there are about 980,000 VHVs covering more than 90% of all villages in Thailand. With continued and unrelenting contact between VHVs and their respective household villagers, the intimate bonding” and “sense-of-belonging” relationship is created. The VHV scheme serves as the backbone of community-based public health service in Thailand. This system is so successful that Thailand is regarded as one of a few developing countries that have efficient primary health care service [5,6].

Should the paramedical personnel be trained to render proper CKD care, it would be interesting whether their intimate relationship and commitment to their responsible village households will result in better outcome when compared with the conventional care. The aim of this study is to compare the effectiveness on delaying CKD progression between a conventional care and an integrated CKD care provided by multidisciplinary team of hospital staffs in conjunction with the community CKD care network (subdistrict health care officers and VHVs).

## Methods

### Study design

The ESCORT study is a community-based, cluster randomized controlled trial. Duration of the study is 2 years. This study has been conducted at Kamphaeng Phet Province, located about 400 kilometers north of Bangkok (Figure 1 and Figure 2). Due to strong relationship among neighboring households in rural communities, it is unable to assign subjects living in the same district to be randomly received either of the 2 CKD care programs without crossover interference from one subject in one household to another. As a result, we have conducted a cluster randomized controlled trial. Two out of eleven districts of the Province, namely Sai Thong Wattana District (control group) and Khlong Khlung District (intervention group), were randomly selected. Details of Public health characteristics of these 2 districts were described in Table 1.

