### Sample size

In a previous observational study, the rate of eGFR decline among diabetic patients with overt nephropathy was 4.2 ± 3.8 ml/min/1.73 m^2^ BSA per year [11]. We hypothesized that if the rate of eGFR decline of intervention group is less than control group at least 1 ml/min/1.73 m^2^ per year, the primary outcome of the study will be interpreted as significant. To acheive 80 percent or higher power to detect the difference between the two treatments, it was estimated that 228 stage 3–4 CKD patients were needed to be enrolled to each group [12]. Taking into account that 15% of patients might be loss to follow-up because of non–end point death or other reasons, approximately 250 patients for each group were required.

According to the inclusion and exclusion criteria, recruitment had done in January to June 2011. About 25% of candidates were eligible and asked to participate in the study. The main reason for non-participation was inability of the patient and caregiver to attend the anticipated visits. In July 2011, 433 patients had been enrolled . Enrolled subjects of each group will be further subdivided into 12 patient subgroups with respect to the vicinity of their subdistrict. Each subgroup will consist of 25–30 CKD patients.

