### Interventions

Two types of CKD care programs will be provided separately according to their respective district of residence. CKD patients residing in district No.8 will be assigned to the control group and those in district No.5 will be assigned to the intervention group (Figure 3). It should be noted that medical facilities in these 2 district hospitals are quite comparable (Table 1). Three investigators who are nephrologists [[name], [name], [name]], will provide essential knowledge about CKD care and treatments according to NKF-K/DOQI guidelines to all staffs of both groups [9].

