## Discussion

Currently, Thailand has a population of approximately 66 million, in which 55 percent of the population live in rural areas [17,18]. In these areas, the number of specialized personnel is limited and work burden is overwhelming, good clinical care and equal accessibility to the care may be too difficult to achieve. Utilizing renal physicians, or even internists, to take care of CKD patients in rural area is rather far from reality. To combat these problems, we try to search for an appropriate CKD care model which could provide optimal treatment to the rural population. To the best of our knowledge, this study is the first large-scale, community-based cluster randomized controlled trial to study the effect of employing an integrated CKD care which is comprised of multidisciplinary CKD care program in conjunction with well-trained paramedical personnel on delaying CKD progression.

In addition to conventional CKD treatment, the two key processes will be added into the intervention group. Firstly, the multidisciplinary team of district hospital staffs will provide demonstration about essential knowledge CKD care during each hospital visit. We hypothesized that this interactive activity will provide better understanding of essential medical knowledge and increase awareness of burden of CKD and ESRD. The second process is quarterly home visit by the CCN. We trained the CCN and endorsed them to work as the escorts (as the abbreviation name of the study) to protect CKD patients. The important roles of CCN is monitoring compliance to the treatments and instantly feedback to the patients. These important informations will be used to modify lifestyle of CKD patients and may improve compliance to the treatments.

Interestingly, the integration of both processes will increase frequency personnel to patients contact compensating for physician to patient contact time which may improve compliance of drug usage and dietary control; furthermore, the continuity of monitoring might be a key mechanism for sustainable self-behavioral modification. We expect the results of this study will set forth a new standard of community-based CKD care for Thailand.

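### With one district per arm, treatment is completely confounded with district, so the primary P-value keeps its 5% error only if eGFR slopes do not vary between districts

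*Protocol article*

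**What the plan says.** The Study design section gives the label and the clusters: "The ESCORT study is a community-based, cluster randomized controlled trial", and "Two out of eleven districts of the Province, namely Sai Thong Wattana District (control group) and Khlong Khlung District (intervention group), were randomly selected". It does not say how the arm was decided between the two districts. The Interventions section makes the allocation explicit: "CKD patients residing in district No.8 will be assigned to the control group and those in district No.5 will be assigned to the intervention group". The reason for allocating by district is contamination, introduced with "Due to strong relationship among neighboring households in rural communities".

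The Sample size section asks for 228 patients per group before loss to follow-up and reports 433 enrolled in total, without a split by arm. The Statistical analysis section compares the rate of eGFR decline with a mixed model or generalized estimating equations (GEE), two-sided, significant below 0.05.

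On the similarity of the districts, the Interventions section says: "It should be noted that medical facilities in these 2 district hospitals are quite comparable (Table 1"). The Discussion closes with: "We expect the results of this study will set forth a new standard of community-based CKD care for Thailand". The limitations section covers contamination, the absence of double-blind individual randomization, guideline teaching in the control arm and the multi-component intervention. It does not say that district and treatment cannot be separated.

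**The concern.** In a cluster randomized trial, chance differences between clusters are part of the error of the treatment comparison. They are estimated from the variation among clusters within each arm. With one cluster per arm there is no such variation to observe. A patient-level P-value then measures only how precisely each district's mean slope is known. It does not measure how far two districts might differ without any intervention.

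Comparing slopes removes fixed differences in eGFR level between the districts. It does not remove differences in slope that arise from case mix, diet, staffing or local practice. At stake is the primary result: a P-value below 0.05 would be read as randomized evidence for the integrated care program, when part or all of the difference could belong to the district.

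**Working it through.** **1. The plan's own sample size.** The inputs are in the Sample size and Statistical analysis sections: "the rate of eGFR decline among diabetic patients with overt nephropathy was 4.2 ± 3.8 ml/min/1.73 m^2^ BSA per year"; a difference as in "if the rate of eGFR decline of intervention group is less than control group at least 1 ml/min/1.73 m^2^ per year"; power 80%; two-sided 0.05.

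- n = 2 × (1.96 + 0.8416)² × 3.8² / 1² = 226.7, so 227 per group. The noncentral-t version gives 228 (power 0.8006).

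The stated 228 is therefore the figure for independent patients. It contains no design effect.

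**2. What the allocation supports.** With k districts per arm, the degrees of freedom for between-district variance are 2k − 2, and the smallest two-sided randomization P is 2 / C(2k, k).

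- At k = 1: 0 degrees of freedom, 2 possible allocations, smallest P = 2/2 = 1.0.

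This needs no assumption about the ICC. Treating the subdistricts (3 against 10 in Table 1) or the 12 patient subgroups as clusters would address correlation inside a district only, because they were not the units allocated.

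**3. Size, as an illustration.** Assumptions: 433 split equally, so m = 216.5 per arm (the article gives only the total); SD 3.8; no loss to follow-up; ICC of the slope not given, so a range is shown.

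- Patient-level SE = 3.8 × √(2/216.5) = 0.365; 95% half-width = 1.96 × 0.365 = 0.72.
- Design effect = 1 + (m − 1) × ICC.
- Error of the nominal 5% test = 2 × [1 − Φ(1.96/√design effect)].
- Half-width with district variance = 0.716 × √design effect.

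| ICC (assumed) | Between-district SD (3.8 × √ICC) | Design effect | Error of nominal 5% test | 95% half-width |
|---|---|---|---|---|
| 0 | 0 | 1 | 5% | 0.72 |
| 0.001 | 0.12 | 1.22 | 7.5% | 0.79 |
| 0.01 | 0.38 | 3.16 | 27% | 1.27 |
| 0.05 | 0.85 | 11.78 | 57% | 2.46 |

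Half-widths are in ml/min/1.73 m² per year, against a target difference of 1.

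**4. Sensitivity to the equal split and to loss.**

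- If 433 were divided in proportion to the Table 1 populations (23,821 and 73,374), the arms would be about 106 and 327. The patient-level variance is 3.8² × (1/106 + 1/327) = 0.180. The total variance is 2 × ICC × 3.8² + (1 − ICC) × 0.180. The errors are about 6.9%, 22% and 51%.
- With equal arms after the 15% loss that the protocol anticipates (216.5 × 0.85 ≈ 184 per arm), the design effects are 1.18, 2.83 and 10.15. The errors are about 7.2%, 24% and 54%.

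The pattern does not depend on either assumption.

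**5. More patients do not help.** With unlimited patients per district, the variance of the difference is still 2 × ICC × 3.8². Even if that variance were known, 80% power for a difference of 1 requires ICC ≤ 1 / [2 × (3.8 × 2.8016)²] = 0.0044.

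**The case against.** The strongest defence has four parts.

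*The label may be literally correct.* A reader might infer that calling the study cluster randomized is false. The article does not support that. It says the two districts were randomly selected and is silent on how the arm was assigned. If the arm was drawn at random between them, clusters were randomized. What lacks support is the inference that the label invites. This part stands.

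*Not every district difference becomes a significant result.* A reader might infer that any pre-existing difference will be reported with P below 0.05. It will not: the observed difference must exceed about 0.72. With SE 0.365, a true pre-existing slope difference of 0.3 crosses that threshold with probability Φ(0.82 − 1.96) + Φ(−0.82 − 1.96) ≈ 13%. The exact statement is that the pre-existing difference is added to the estimate. This part stands too.

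*The arms share a good deal.* Staff of both groups receive the same nephrologist teaching, the treatment targets and visit schedule are common, and each arm's study care has two general practitioners and two chronic care nurses. Several Table 1 rows match: share of farmers, nurses and officers per subdistrict office, and volunteers per village. These features may reduce the difference between districts, but they cannot show that it is zero.

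*Table 1 does not prove bias.* A reader might take it as evidence that the districts' outcomes differ in a known direction. It is not. The comparability sentence concerns hospital facilities, and population is not a facility. The nutritionist count of 0 against 1 is partly the treatment contrast, because the nutritionist belongs to the intervention team. Hospital headcounts are higher in the intervention district. Per 10,000 residents, general practitioners (3/2.3821 = 1.26 against 5/7.3374 = 0.68) and nurses (10.5 against 7.4) are more numerous in the control district. The sentence is loosely worded, but that is secondary to the main point.

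**Conclusion.** The point holds. Treatment and district are completely confounded, between-district slope variance has 0 degrees of freedom, and the 0.05 rule keeps its stated error only if that variance is zero. This follows from the allocation alone, and a fuller analysis plan could not change it. The article does not disclose it as a limitation.

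The size is illustrative. Under equal arms of 216.5, SD 3.8, no loss to follow-up and an assumed ICC of 0.001, 0.01 or 0.05, the error is about 7.5%, 27% or 57%, and the half-width rises from 0.72 to 0.79, 1.27 or 2.46. A reader might take these as the trial's actual error rates. They are not, because the article gives no ICC.

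**What to change.** Enrolment is complete, so the changes are to wording and reporting.

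- **Abstract, Study design, Discussion and Limitation of the study:** wherever the design is called cluster randomized, add that there is one district per arm.
- **Limitation of the study:** state that district and treatment effects cannot be separated, and that a slope difference already present between the districts would be included in the estimated effect.
- **Statistical analysis:** present the primary P-value and interval as conditional on no between-district slope variance. Beside them, give a sensitivity table whose variance adds 2 × the between-district variance over an assumed ICC range, for example 0.001, 0.01 and 0.05.
- **Discussion:** limit the conclusion to a comparison of these two districts.
- **Interventions:** replace the comparability sentence with the hospital staffing differences in Table 1, control against intervention: general practitioners 3 and 5, nurses 25 and 54, pharmacists 2 and 5, nutritionists 0 and 1.

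The cost is a few sentences and one table, with no new patients. The downside is a less favourable claim.

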**Figure 1 F1:**
[figure not shown]
Map of Thailand.

**Figure 2 F2:**
[figure not shown]
**Map of Kamphaeng Phet Province.** The numbers represent respective districts of the Province. District No.5 and No.8 denote Khlong Khlung District (Intervention group) and Sai Thong Wattana District (Control group), respectively.

**Table 1 T1:** Public health data of the 2 districts under the study

	**Control group**	**Intervention group**
Total population	23,821	73,374
Occupation: farmer (%)	80	80
No. of subdistricts	3	10
No. of villages	38	103
No. of personnel at the district hospitals		
• General practitioners	3	5
• Nurses	25	54
• Pharmacists	2	5
• Nutritionists	0	1
No. of personnel at each subdistrict health office		
• Nurses	1	1
• Subdistrict health care officers	3-5	3-5
No. of village health volunteers per village	10-12	10-12

### Enrollment

The study was approved by the Ethics Committee of Institutional Review Board of Ministry of Public Health, Thailand and was registered with http://www.clinicaltrials.gov (NCT01978951). Written inform consents were obtained prior to recruitment. The study was conducted in accordance with good clinical practice and the Declaration of Helsinki [7]. Eligible cases are those who live in these 2 districts, age of 18–70 years old and had diabetes and/or hypertension. Patients whose eGFR was in a range of 15–59 ml/min/1.73 m^2^ body surface area estimated twice at 3 months apart were asked to participate in this study. Creatinine-based estimated glomerular filtration rate (eGFR) was calculated with the CKD-EPI equation [8]. Patients were excluded if they have any of the following: unstable/advanced cardiovascular disease, obstructive uropathy, ESRD, HIV infection, pregnancy, body mass index (BMI) less than 18 or more than 40 kg/m^2^, being under treatment for malignancy, urine protein-creatinine ratio more than 3.5 g/g creatinine and active urinary sediment (urine red blood cells more than 3 cells/high power field or urine white blood cells more than 10 cells/high power field). Hypertension was defined as a systolic blood pressure higher than 140 mmHg or a diastolic blood pressure higher than 90 mmHg or concomitant use of antihypertensive medications [9]. Blood pressure was recorded twice with a sphygmomanometer with 15-minute rest between the measurements. Diabetes was diagnosed when a fasting plasma glucose is at or above 126 mg/dl or HbA1C at or above 6.5 percent twice after repeated measurements [10].

### Sample size

In a previous observational study, the rate of eGFR decline among diabetic patients with overt nephropathy was 4.2 ± 3.8 ml/min/1.73 m^2^ BSA per year [11]. We hypothesized that if the rate of eGFR decline of intervention group is less than control group at least 1 ml/min/1.73 m^2^ per year, the primary outcome of the study will be interpreted as significant. To acheive 80 percent or higher power to detect the difference between the two treatments, it was estimated that 228 stage 3–4 CKD patients were needed to be enrolled to each group [12]. Taking into account that 15% of patients might be loss to follow-up because of non–end point death or other reasons, approximately 250 patients for each group were required.

According to the inclusion and exclusion criteria, recruitment had done in January to June 2011. About 25% of candidates were eligible and asked to participate in the study. The main reason for non-participation was inability of the patient and caregiver to attend the anticipated visits. In July 2011, 433 patients had been enrolled . Enrolled subjects of each group will be further subdivided into 12 patient subgroups with respect to the vicinity of their subdistrict. Each subgroup will consist of 25–30 CKD patients.

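### The 228 per group is the sample size for independent patients, so the stated 80% power holds only if there is no variation between the two districts (ICC = 0)

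*Protocol article*

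**What the plan says.** The Study design section of the protocol article describes the trial in these words: "The ESCORT study is a community-based, cluster randomized controlled trial". It names the units: "Two out of eleven districts of the Province, namely Sai Thong Wattana District (control group) and Khlong Khlung District (intervention group), were randomly selected". The Interventions section confirms that residence alone decides the arm: "CKD patients residing in district No.8 will be assigned to the control group and those in district No.5 will be assigned to the intervention group". There is thus one cluster per arm.

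The Sample size section works with patients. It takes its variability from an observational study in which "the rate of eGFR decline among diabetic patients with overt nephropathy was 4.2 ± 3.8 ml/min/1.73 m^2^ BSA per year", and it sets the target as "if the rate of eGFR decline of intervention group is less than control group at least 1 ml/min/1.73 m^2^ per year". For power of at least 80% it concludes that "it was estimated that 228 stage 3–4 CKD patients were needed to be enrolled to each group". It then rounds up to about 250 per group for 15% loss to follow-up, which is the only inflation mentioned. It later reports 433 patients enrolled by July 2011. The Statistical analysis section sets two-tailed tests at 0.05.

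**The concern.** The unit of allocation is the district, but the sample size is expressed in patients and uses a patient-level SD. If mean eGFR slopes differ between districts for any reason other than the intervention, that difference goes straight into the treatment comparison. The variance of the comparison then has a between-district part that is not divided by the number of patients. A calculation for independent patients sets this part to zero.

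The power claim is what justifies the sample size for the primary outcome. If it rests on an unstated assumption of no district variation, a null result could be read as the result of a trial with 80% power when the real power may be much lower.

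**Working it through.** **Inputs.** SD of slope 3.8 and difference 1 ml/min/1.73 m² per year, power 80%, 228 per group, 433 enrolled (Sample size); two-sided 0.05 (Statistical analysis); one district per arm (Study design, Interventions). The ICC, meaning the share of slope variance that lies between districts, is not in the article. The values below are assumptions.

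**Step 1: reproduce 228.** The normal approximation is n = 2(1.960 + 0.842)² × 3.8² / 1² = 226.7, so 227. The t-test version gives 227.64, so 228. This matches the article to the patient. A one-sided test would give 179, which does not match. A design effect above 1 would have produced a larger number, so none was applied.

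**Step 2: power with district variance.** With one district of m patients per arm, total SD held at 3.8 and the ICC treated as known:

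- design effect DE = 1 + (m − 1) × ICC
- SE = 3.8 × √(2 × DE / m)
- power = Φ(1/SE − 1.96) + Φ(−1/SE − 1.96)

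For m = 228:

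| ICC (assumed) | DE | SE | Power |
|---|---|---|---|
| 0 | 1.00 | 0.356 | 80% |
| 0.001 | 1.23 | 0.394 | 72% |
| 0.005 | 2.13 | 0.520 | 49% |
| 0.01 | 3.27 | 0.644 | 34% |
| 0.05 | 12.35 | 1.251 | 13% |

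**Step 3: can more patients help?** As m grows, SE falls only to 3.8 × √(2 × ICC). For 80% power SE must be at most 1/2.80 = 0.357, which requires ICC ≤ 0.357² / (2 × 3.8²) ≈ 0.0044. Below that limit, more patients do work: n = 227(1 − ICC) / (1 − 227 × ICC) gives about 294 per group at ICC 0.001 and about 415 at ICC 0.002. Above it, no number is enough. At ICC 0.01 the limiting SE is 0.537 and the ceiling is 46%.

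**Step 4: the number enrolled.** The article does not give the split of the 433. If equal, it is 216.5 per arm. By the same formulas, before any loss to follow-up:

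| ICC (assumed) | Power at 216.5 per arm |
|---|---|
| 0 | 78% |
| 0.001 | 70% |
| 0.005 | 48% |
| 0.01 | 34% |
| 0.05 | 13% |

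After 15% loss, 216.5 × 0.85 = 184 per arm, and power at ICC 0 is about 71%.

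**Direction of error.** Steps 2 to 4 treat the between-district variance as known. With one district per arm there are 0 degrees of freedom to estimate it, so the figures are optimistic.

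**The case against.** The strongest reply is that the ICC is unknown. The true value could be close to zero, and then the loss of power would be small. That stands, and it means that no single figure in the table can be called the trial's power. It does not rescue the claim, because a power that depends on an unknown quantity cannot be stated without condition, and even ICC 0.001 takes it to 72%.

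It could also be said that a journal article condenses its protocol. Here the inputs and the result are both printed, and the result equals the answer without clustering. A fuller document could discuss the ICC, but it could not make 228 a clustered figure.

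Recruitment is reported as complete, so the correction changes no design and no data. That is true. It changes what the stated power can be taken to mean.

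Three stronger readings are tempting, and the article does not support them:

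- *More patients could never restore the power.* This is true only above an ICC of about 0.0044. Below it they could, as step 3 shows.
- *The article itself concedes that outcomes are correlated.* The Study design section does give a reason that begins "Due to strong relationship among neighboring households in rural communities", but the reason concerns crossover of the care programmes between households, that is, contamination. It says nothing about correlation of eGFR slopes and is not evidence for any ICC.
- *The 12 patient subgroups per group are the clusters and should carry the calculation.* They were not the units of allocation. Their stated size of 25–30 also implies at least 24 × 25 = 600 patients, against 433 enrolled. No subgroup-level power is offered here, and the district result does not depend on it.

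**Conclusion.** The point holds in this form: 228 per group is the two-sample t-test number for independent patients, it contains no design effect, and the 80% power holds only at ICC = 0. Under the assumed ICCs of 0.001 to 0.05, power with 228 evaluable patients per arm runs from 72% down to 13%, and 80% is out of reach in these two districts once the ICC exceeds about 0.0044. The reproduction of 228 rests only on the article's own inputs. The size of the loss rests on the assumed ICCs, a total SD of 3.8 and a district variance treated as known. The article does not show that power is in fact low. It shows that the stated power depends on an assumption it does not declare.

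**What to change.** In the Sample size section, replace the unconditional claim of at least 80% power with a sentence such as: *228 evaluable patients per group gives 80% power only if outcomes are independent within district (ICC = 0).*

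Add a short power table for the number actually enrolled, with the ICCs labelled as assumptions, the arm sizes stated (step 4 assumes an equal split), and a note that one district per arm leaves 0 degrees of freedom to estimate the district variance. Give the ICC 0 row both before and after 15% loss (about 78% and 71%).

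The cost is one sentence and one table. No data or analysis change, but the stated power becomes less favourable.

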### Statistical analysis

Analysis of the primary outcome will be based on an intention-to-treat basis. Descriptive statistics will be expressed as the mean and standard deviation. Discrete variables will be presented as frequency and percentage. An independent t-test will be applied to compare mean values and mean differences between intervention and control groups. Differences between categorical variables will be analysed with Chi-square or Fisher’s exact tests. The comparison of the rate of eGFR decline will be analyzed using linear mixed models (Generalized Estimating Equation) [16]. The difference of incidence of clinical endpoints will be analysis using Cox-regression analysis. All statistical tests will be two-tailed tests. A P-value of less than 0.05 will be considered statistically significant. The data will be analysed using SPSS 16.0 (SPSS Inc., Chicago, IL, USA).

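### The allowance for 15% loss needs 269 patients per group, not about 250, and the 433 enrolled fall short of 80% power even with no loss

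*Protocol article*

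**What the plan says.** The Sample size section of the protocol article takes a standard deviation of 3.8 ml/min/1.73 m² per year from an earlier observational study and a difference of 1 between groups. The aim is stated as "To acheive 80 percent or higher power to detect the difference between the two treatments", and the result is 228 per group. After an allowance for 15% loss to follow-up, the section concludes: "or other reasons, approximately 250 patients for each group were required".

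The section places recruitment in January to June 2011 and then reports: "In July 2011, 433 patients had been enrolled". The abstract says instead: "Approximatly 500 stage 3–4 CKD patients from 2 districts were enrolled". No count per arm and no revised power are given.

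The section also divides each group into 12 subgroups by locality: "Each subgroup will consist of 25–30 CKD patients". It describes the target difference in these words: if decline in the intervention group is "less than control group at least 1 ml/min/1.73 m^2^ per year, the primary outcome of the study will be interpreted as significant".

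The Statistical analysis section sets the test criterion: "All statistical tests will be two-tailed tests" and "A P-value of less than 0.05 will be considered statistically significant".

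**The concern.** Three sets of figures do not fit together.

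- The step from 228 to about 250 does not correspond to the 15% loss that it is said to cover.
- The number enrolled differs between the abstract and the Sample size section, and the lower number is below the target before any loss.
- The subgroup plan implies a total well above either enrolment figure.

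The first two bear on the primary outcome. Anyone interpreting a null result would rely on 80% power for a difference of 1, which the protocol's own inputs do not deliver. The third matters for the 24-hour urine sub-study, which the Laboratory analysis section draws from two of the twelve subgroups in each group.

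The sentence about a difference of at least 1 being interpreted as significant adds a lesser difficulty, because it can be mistaken for a second criterion beside the P-value.

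**Working it through.** **Inputs.** Difference 1, SD 3.8, power 80%, loss 15% and 433 enrolled come from Sample size. The two-sided 5% level comes from Statistical analysis. District populations of 23,821 and 73,374 come from Table 1.

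**1. Reproduce 228.** n per group = 2 × (1.960 + 0.842)² × 3.8² / 1² = 226.7, so 227 by the normal approximation. The two-sample t-test gives 227.6, so 228. The stated figure reproduces, which confirms the inputs and shows that no clustering term was included.

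**2. Allowance for loss.**
- Dividing by the retained fraction: 228 / 0.85 = 268.2, so 269 per group and 538 in total.
- The common shortcut of multiplying: 228 × 1.15 = 262.2, so 263.
- Loss that 250 can absorb: 1 − 228/250 = 8.8%.
- Evaluable at 250 with 15% loss: 250 × 0.85 = 212.5 per group, with power about 77%.

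Neither method gives about 250. The gap from 269 is 19 per group, or 38 in total.

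**3. Enrolment.** 433 is 67 below 500, 105 below 538, and 23 below 2 × 228 = 456.

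**4. Power at 433, unclustered, true difference 1.** The standard error of the difference is 3.8 × √(1/n₁ + 1/n₂). The detectable difference is the one found with 80% power.

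| Split | Loss | n per arm | Power | Detectable difference |
|---|---|---|---|---|
| Equal | none | 216.5 / 216.5 | 78% | 1.03 |
| Equal | 15%, contributing nothing | 184 / 184 | 71% | 1.11 |
| By district population (assumed) | none | 106 / 327 | 65% | 1.19 |
| By district population (assumed) | 15%, contributing nothing | 90 / 278 | 58% | 1.29 |

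The population ratio is 73,374 / 23,821 = 3.08. The equal split is the most favourable allocation for a given total. At 2:1 the power is 73% with no loss and 66% with 15% loss.

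**5. Subgroups.** 12 × 25 = 300 and 12 × 30 = 360 per group, so 600 to 720 in total. If 12 was meant to cover both groups together, the total is 300 to 360. Neither range contains 433 or 500.

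**The case against.** **Is 71% the power of the trial?** A reader might infer that 80% should simply be replaced by 71%. The document does not support that. The figure assumes an equal split, which is nowhere stated, and that lost patients supply no information. The Statistical analysis section plans an intention-to-treat comparison of slopes by mixed model or GEE, Table 4 schedules creatinine at every visit, and laboratory tests are also planned at withdrawal. Patients lost partway would therefore contribute data, so 71% to 78% is the fair range for an equal split. This objection stands, but even the top of the range is below 80%.

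**Clustering.** Each arm is one district, so no unclustered figure can be presented as the achieved power. This also stands: the figures show only what the protocol's own method yields at 433.

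**Subgroup size.** It is tempting to divide 433 by 24 and say that subgroups hold about 18 patients, and that the urine sample is about 36 per group. That is only an average over both arms. At the population split, the intervention arm would average 327/12 = 27, within the planned range, and the control arm about 106/12 = 9. The planned size cannot hold in both arms, but the true sizes cannot be derived without arm counts.

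**A second significance rule.** A reader might infer that an observed difference of 1 is a decision rule competing with P < 0.05. The sentence is framed as a hypothesis, sits among the sample-size assumptions, and the 228 was computed by treating 1 as the assumed effect. It is best read as a loosely worded target difference, and only the wording needs attention.

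**Practical effect.** Recruitment is over, so 269 cannot now be recruited to. That limits the remedy to reporting and does not make the stated derivation correct.

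**Conclusion.** The point holds in this form. On the protocol's own inputs, 15% loss requires 269 per group, and about 250 is too few by 19; the word approximately does not cover that gap. The abstract's enrolment figure contradicts the Sample size section. With 433 enrolled, the stated power of 80% or more is not reached under any allocation or loss assumption. With equal arms it is about 78% with no loss and 71% if 15% contribute nothing. It is lower with unequal arms, for example 65% to 58% if enrolment followed district populations, which is an assumption.

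The under-allowance and the enrolment shortfall are separate contributions. At 15% loss the first alone brings power to 77%, and the second takes it to 71% with equal arms. All these figures rest on SD 3.8, a true difference of 1 and no allowance for clustering, so they are upper bounds.

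The subgroup figures are inconsistent with enrolment, but the correct sizes are unknown. The sentence on significance is a minor wording point. These are conflicts between figures that the article itself prints, so they are not details left to a fuller protocol or analysis plan.

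**What to change.** - In Sample size, acknowledge that the stated 15% loss requires 269 per group, and that about 250 covers 8.8%.
- In the abstract, replace the figure of about 500 by 433, and report the number enrolled in each arm.
- Replace the 80% power claim by the power and detectable difference recomputed for the actual arm counts. Label both as ignoring clustering, so that the power reads as an upper bound, and state how lost patients are treated in the calculation.
- Report the actual number and size of the subgroups in each arm, in place of 12 subgroups of 25 to 30, without substituting an average of 18. Give the resulting size of the 24-hour urine sample.
- Reword the sentence on 1 ml/min/1.73 m² per year as the assumed true difference, leaving P < 0.05 as the only significance criterion.

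These are changes to text and reported counts; conduct and analysis are unaffected. The cost is that the stated power becomes less favourable.
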